### Statistical hypotheses, methods, and analyses

The primary endpoint (differences in the blood pressure control rate between intervention and control group) will be analyzed using a chi-square test. A *P* value <0.05 will be considered significant.

For analyses of secondary endpoints, average blood pressure levels at baseline and at follow-up will be determined for all study patients and separately for patients of both study arms. Differences between baseline and follow-up will be tested for significance within each study arm using paired t-tests. Differences in the mean systolic and diastolic blood pressure level of patients of the intervention group and patients of the control group will be tested for significance using an adjusted t-test for independent samples, which accounts for the intra-cluster correlation [6].

The analysis will determine which elements of hypertension management have been implemented into everyday routine during the study period and which of them are regarded as being helpful. To describe the effect of single hypertension management strategies on blood pressure, bivariate analyses will be conducted.

A generalized linear mixed model will be performed to identify predictors on blood pressure control at follow-up. The model will include patient level covariates such as age, sex, lifestyle, comorbidities, and changes in each patient’s hypertension management as well as cluster-level covariates such as changes of hypertension-related diagnostic and therapeutic strategies. Modeling will account for cluster effects by random effects modeling. Statistical analyses will be performed using IBM SPSS Statistics for Windows, Version 22.0 (Armonk, New York: IBM Corp.).

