## Methods/Design

### Study design

The study is designed as a cluster randomized trial with primary care practices as the unit of randomization. The cluster design is used because the intervention (education) addresses practice teams, and thereby aims to improve patient outcomes indirectly [5]. Additionally, this design takes into account that patients of a certain practice may be more homogenous regarding medical and sociodemographic characteristics than patients of other practices [5,6]. Each practice cluster includes five patients at minimum.

Practices from both arms will receive the intervention, but sequentially, with control practices receiving the intervention after the follow-up data collection in both study groups.

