### Sample size calculation

For the primary endpoint, a blood pressure control rate of 35% is assumed for the control group, while a blood pressure control rate of 70% is assumed for the intervention group [8,9]. Assuming an equal number of clusters per study arm, an average cluster size of five patients and an intraclass correlation coefficient of 0.05 [5], ten clusters per study arm are needed to detect the assumed effect using a chi-square test with a two-sided significance level of 5% and a power of 80%. Sample size calculation was performed in R package CRTSize, function n4props [10].

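### The primary chi-square test carries no adjustment for clustering although practices were randomised, so its nominal 5% type I error is about 9% at the planning ICC and enrolled practice sizes

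*Protocol article*

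**What the plan says.** All places are in the Methods/Design part of the protocol article.

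- **Study design:** "The study is designed as a cluster randomized trial with primary care practices as the unit of randomization". The section justifies this partly by patients within a practice being more alike than patients of different practices.
- **Sample size calculation:** uses "an average cluster size of five patients and an intraclass correlation coefficient of 0.05". The planned contrast is 35% controlled without the education against 70% with it. The test is called a chi-square test, at two-sided 5% and 80% power, and the result is ten practices per arm.
- **Statistical hypotheses, methods, and analyses, primary endpoint:** "The primary endpoint (differences in the blood pressure control rate between intervention and control group) will be analyzed using a chi-square test". No clustering adjustment is mentioned, and the threshold for significance is set at 0.05.
- **Same section, secondary endpoints:** mean blood pressure is compared between arms by an "adjusted t-test for independent samples, which accounts for the intra-cluster correlation".
- **Same section, mixed model:** a generalized linear mixed model with random effects is planned to identify predictors of control at follow-up. Its covariates include changes in patients' management and in practice strategies.

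**The concern.** A standard chi-square test on patients assumes independent observations. Patients of one practice share a physician, and here they also share whatever the practice chose to adopt from the education. With a positive ICC, the difference in control rates between arms varies more than the test assumes. The test then rejects a true null hypothesis more often than 5% of the time, and any confidence interval built on the same variance is too narrow.

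Allowing for the ICC in the sample size does not prevent this. It protects power, while the error rate depends on the test that is run. Sample size and analysis therefore rest on different assumptions.

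At stake is the trial's main claim: a primary result just below P = 0.05 would not carry the stated error rate.

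**Working it through.** **Inputs**

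- 24 practices, 12 per arm (Practice and patient recruitment).
- 169 patients, 101 of them in the intervention arm, so 68 in control (Inclusion and exclusion criteria for patients).
- Planned size 5 per practice, ICC 0.05, rates 35% and 70% (Sample size calculation).
- At least five patients per practice (Study design).

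**1. The plan's own figure.** With unpooled variance, n per arm = (1.96 + 0.842)² × (0.35×0.65 + 0.70×0.30) / 0.35² = 28.03. The planning design effect is 1 + (5 − 1)×0.05 = 1.20, so 28.03 × 1.20 / 5 = 6.73, or 7 practices per arm. Other common variants give 8 (pooled variance, or t quantiles) or 9 (pooled with continuity correction). None gives the stated ten at 80% power; ten practices of five give about 91%. The difference is on the safe side for power and does not bear on the error rate of the test.

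**2. Practice sizes as enrolled.**

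- Overall: 169/24 = 7.04
- Intervention: 101/12 = 8.42
- Control: 68/12 = 5.67

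**3. Design effects at ICC 0.05**, from DE = 1 + (m − 1) × ICC:

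- Overall: 1 + 6.04×0.05 = 1.302
- Intervention: 1 + 7.42×0.05 = 1.371
- Control: 1 + 4.67×0.05 = 1.233
- Arms combined by their variance contributions: (1.371/101 + 1.233/68) / (1/101 + 1/68) = 1.289

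**4. True type I error of the unadjusted test**, from α = 2 × [1 − Φ(1.96/√DE)]:

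| Setting | ICC | DE | True α |
|---|---|---|---|
| Planned, 5 per practice | 0.05 | 1.200 | 7.4% |
| Enrolled, arm-specific means | 0.05 | 1.289 | 8.4% |
| Enrolled, overall mean 7.04 | 0.05 | 1.302 | 8.6% |
| Enrolled, overall mean 7.04 | 0.01 | 1.060 | 5.7% |
| Enrolled, overall mean 7.04 | 0.10 | 1.604 | 12.2% |

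For the third row, 1.96/√1.302 = 1.718, which gives 0.0859.

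**5. Simulation check.** Beta-binomial data, null rate 35%, ICC 0.05, 200,000 trials per setting:

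- 101 and 68 patients spread evenly over 12 + 12 practices: 8.7%.
- An assumed uneven split with at least five per practice (intervention 5, 5, 5, 5, 5, 6, 8, 9, 10, 12, 14, 17; control nine practices of 5, then 6, 7, 10): 9.3%.
- Planned 10 × 5 per arm: 7.4%.
- No clustering: 5.0%, so the excess comes from clustering alone.

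**6. What adjustment changes.** Dividing the chi-square statistic by 1.302 is the same as using a critical value of 3.841 × 1.302 = 5.00. On the unadjusted scale that corresponds to P of about 0.025, since 1.96 × √1.302 = 2.236. Unadjusted P values between about 0.025 and 0.05 would be called significant when the adjusted test would not. Intervals should be wider by √1.302 = 1.14, or 14%. Power of the adjusted test for 35% against 70% is about 98% at the enrolled numbers and about 91% at 10 × 5 per arm.

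**The case against.** **An adjusted test may be meant.** The analysis section never says the chi-square is unadjusted. The sample size section uses the same name for a calculation that includes an ICC and was done in a package for cluster trials. This is possible, but the analysis section marks its adjustment explicitly for the secondary t-test and for the mixed model, and not for the primary test. An analyst following the text would run the standard test. If adjustment was intended, the sentence still has to say so.

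**The size is conditional.** This stands. The ICC of 0.05 is a planning value, and the distribution of practice sizes is not reported. With a minimum of five, only 68 − 60 = 8 control patients lie above the minimum, so extreme imbalance in that arm is not possible. The 169 are baseline enrolments, and loss to follow-up would shrink the clusters and the inflation. At five per practice it would still be 7.4%.

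**The mixed model accounts for clustering.** It does, and its covariate list is only illustrative, so study arm is not ruled out. But it is not tied to the primary hypothesis, and it conditions on management changes after randomisation through which the intervention is meant to work. The Discussion adds that its terms will be selected from bivariate results. It cannot stand in for the arm comparison.

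**No confidence interval is planned for the primary endpoint.** Correct. The remark on width applies only to an interval computed on the same basis as the test.

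**A large effect would be detected anyway.** If the assumed 35 percentage points are real, adjustment will hardly matter. It matters if the effect is absent or small, which is when a type I error rate is needed.

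**Conclusion.** The point holds and must be fixed. As written, the test deciding the primary endpoint ignores the unit of randomisation, and no other part of the article supplies the adjustment. At the planning ICC and the enrolled practice sizes, the true two-sided error is about 8.4% to 9.3% instead of 5%, depending on how evenly patients are spread over practices. It is 7.4% at the planned five per practice. If the ICC were as low as 0.01 the inflation would be slight. These figures assume the same ICC in both arms and follow-up sizes close to enrolment. The direction does not depend on them: any positive ICC raises the error above 5%.

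**What to change.** Replace the sentence on the primary test and fix one method before the analysis. Suggested wording, closest to the sample size section:

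> *The control rates of the two arms will be compared with a chi-square test adjusted for clustering by practice, with the ICC estimated from the trial data. The difference in rates will be reported with a 95% confidence interval using the same adjustment.*

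A mixed logistic model with study arm, a practice random intercept and small-sample degrees of freedom (24 − 2 = 22) is equally acceptable. If it is chosen, name it instead of the chi-square and state the effect measure, because the model gives an odds ratio and not directly a difference in rates. Either way, the unadjusted chi-square should not be the decision test, and the primary model should not contain changes in management after randomisation.

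The cost is one sentence and somewhat larger P values. A random-effects model is already planned in the named software, and the adjusted chi-square needs only the standard statistic and an ICC estimate. By the Trial status section, data management was still under way and results were awaited, so the test can be settled before the analysis.

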### Inclusion and exclusion criteria for patients

Patients are eligible for recruitment if 1) they are ≥18 years old and 2) their blood pressure is uncontrolled according to current guidelines: ≥140/90 mmHg in office readings, and/or ≥130/80 mmHg in 24-hour ambulatory measurements (based on the average 24-hour blood pressure), and/or ≥135/85 mmHg in patient self-measurements at home (based on the mean of a one-week protocol with at least two measurements daily) [7]. Patients with and without hypertension-related diseases such as angiographically proven coronary disease, peripheral or cerebral vascular disease, and/or high risk conditions such as diabetes can be recruited. All patients must be able to give informed consent and to read and comprehend the German language. Patients fulfilling all of these criteria are asked for study participation, receive written information about the study, and sign an informed consent form. A total of 169 patients were enrolled at baseline; of these, 101 (59.8%) were associated with the intervention arm.

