### Outcome measures

The primary endpoint of the study is the change of the blood pressure control rate, defined as percentage of patients with an average 24-hour blood pressure <130/80 mmHg. The key secondary endpoints are the changes in average systolic and/or diastolic blood pressure (in mmHg) and changes in practice-specific hypertension management stratified by the intervention status of the practice. All outcomes are measured at baseline (before the intervention) and at follow-up (3 months after the last education session) in both study arms. This results in an average follow-up period of 5 months per patient.

To determine the interventional effectiveness on the patients’ level, each study patient receives a 24-hour ambulatory blood pressure monitoring at baseline and at follow-up. To control for confounding, general practitioners complete a questionnaire on medical characteristics of each study patient (for example, diagnosis, comorbidities, medication, and differential diagnoses). Study patients complete a self-administered paper and pencil questionnaire on individual characteristics such as sociodemographic characteristics, risk factors (for example, physical activity and smoking behavior), medication adherence, and management of blood pressure self-readings at baseline and follow-up.

At baseline, general practitioners complete a questionnaire on personal characteristics (age, sex), medical degree(s), additional qualifications, and individual attitudes toward hypertension treatment (motivation and self-efficacy). To determine practice changes after intervention, the follow-up questionnaire focuses on changes in daily practice routines and determines which of the hypertension management strategies are implemented by the practices.

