### Control group

General practitioners of the control group are offered the same education sessions, but only after completing the follow-up data collection in both study arms. Control group patients receive treatment as usual.

Despite this sequential design, it cannot be excluded that study participation, 24-hour blood pressure measurement at baseline and follow-up, and completing a questionnaire at baseline and follow-up might influence the physicians’ and patients’ awareness for hypertension in both study arms.

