### Trial status

The study began in September 2013. Baseline data collection was completed in January 2014. Follow-up data collection was completed in August 2014. Data management, including quality control, is ongoing. Results are expected in summer 2015.

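### The within-arm paired t-tests of blood pressure change ignore clustering and cannot isolate the intervention; the cluster-adjusted between-arm comparison should carry all inference on change

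*Protocol article*

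**What the plan says.** For the secondary endpoints, the section on statistical hypotheses, methods and analyses of the protocol article states: "Differences between baseline and follow-up will be tested for significance within each study arm using paired t-tests". It does not call these tests descriptive and attaches no allowance for clustering. The next sentence compares mean systolic and diastolic levels between the arms with an "adjusted t-test for independent samples, which accounts for the intra-cluster correlation".

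Under Outcome measures, the key secondary endpoints include changes in average blood pressure, and "each study patient receives a 24-hour ambulatory blood pressure monitoring at baseline and at follow-up". Under the inclusion criteria, patients can enter if "their blood pressure is uncontrolled according to current guidelines: ≥140/90 mmHg in office readings, and/or ≥130/80 mmHg in 24-hour ambulatory measurements", or on home self-measurements of at least 135/85 mmHg. Under Control group, the article says it cannot be excluded that study participation, the 24-hour measurements and the questionnaires "might influence the physicians’ and patients’ awareness for hypertension in both study arms".

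**The concern.** There are two separate difficulties.

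First, a plain paired t-test treats all patients in an arm as independent. The Study design section justifies cluster randomization partly by the similarity of patients within a practice, and the sample size uses an intraclass correlation of 0.05. If changes are correlated within practices, the standard error is too small and the stated 5% level is not kept.

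Second, a within-arm P value tests whether mean blood pressure moved, not whether the education moved it. Selection for uncontrolled readings and the effects of participation can produce a fall in either arm.

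The wording makes this more than a side issue. The endpoint is a change, but the between-arm test is worded on the mean level. The paired tests are therefore the only ones worded on change from baseline, and a reader looking for the result on that endpoint would go to them.

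**Working it through.** The article gives no figure for the paired tests, so there is none to reproduce.

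**Inputs from the article.** 24 practices in two arms of equal size, so 12 per arm. 169 patients, 101 of them in the intervention arm, so 68 controls. Intraclass correlation (ICC) 0.05, stated for the control-rate endpoint. **Assumptions.** All 12 practices per arm recruited, cluster sizes are equal, there is no loss to follow-up, and the ICC of the change scores lies between 0.01 and 0.10.

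**Step 1: type I error with clustering ignored.** Mean cluster size m is 101/12 = 8.42 and 68/12 = 5.67. The design effect is DE = 1 + (m − 1) × ICC. The true two-sided error of a nominal 5% test is about 2 × [1 − Φ(1.96/√DE)].

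At ICC 0.05:
- Intervention: DE = 1 + 7.42 × 0.05 = 1.37, and 1.96/√1.37 = 1.67, giving 9.4%.
- Control: DE = 1 + 4.67 × 0.05 = 1.23, and 1.96/√1.23 = 1.76, giving 7.8%.

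| ICC of change | DE, intervention / control | True error, intervention / control |
|---|---|---|
| 0.01 | 1.07 / 1.05 | 5.9% / 5.5% |
| 0.05 | 1.37 / 1.23 | 9.4% / 7.8% |
| 0.10 | 1.74 / 1.47 | 13.8% / 10.6% |

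Simulation agrees: 9.3% and 7.8% at ICC 0.05, and 13.9% and 10.8% at 0.10.

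**Step 2: regression to the mean with no intervention effect.** If every patient qualified on the same 24-hour systolic reading that serves as baseline, the expected fall is (1 − r) × SD × φ(a)/[1 − Φ(a)], with a = (130 − mean)/SD and r the retest correlation. For example, assume mean 130, SD 12 and r = 0.8. Then a = 0, the ratio is 0.798, and the fall is 0.2 × 12 × 0.798 = 1.91 mmHg. With a change-score SD of 7.3, fall over standard error is 1.91/(7.3/√101) = 2.63 and 1.91/(7.3/√68) = 2.16. The chance of a significant fall is then about 74% and 56%, and in both arms 0.737 × 0.563 = 41%.

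The result depends strongly on the route of entry. All distributions below are assumed.

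| Route of entry | Expected fall (mmHg) | Significant fall, per arm | Both arms |
|---|---|---|---|
| Same 24-hour reading (mean 125–135, SD 12–15, r 0.6–0.9) | 0.7–6.1 | 24–99.9% (n = 101), 17–99% (n = 68) | 4–99% |
| Office or 24-hour reading (office mean 140, SD 18, correlation with 24-hour 0.55; r 0.65–0.9) | 0.4–1.5 | 8–28% | about 1–6% |
| Separate office reading only | about 0 | 2–5% | about 0.1–0.2% |

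The article gives neither the share of patients by route nor whether a qualifying 24-hour reading also serves as baseline. Entry on home readings alone was not modelled.

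**The case against.** The ICC of 0.05 belongs to the control rate, and pairing removes stable differences between practices, so the ICC of change may be smaller. That stands, and it is why a range is given. But the direction is not in doubt for any positive value, and the Discussion itself expects variation between practices because each chooses its own strategies.

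The article also says nowhere that within-arm P values will be used to claim effectiveness. The abstract puts the focus on differences between the groups, the adjusted between-arm test follows directly, and the primary endpoint is untouched. That limits the consequence to misreading of a secondary analysis.

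Three stronger readings are tempting but not supported:
- A reader might infer that regression to the mean alone makes both arms likely to be significant. The outcome is 24-hour pressure while entry may rest on office or home readings, and the computed chance runs from about 0.1% to 99%.
- A reader might infer that a fall significant only in the larger intervention arm is likely under no effect. At mean 130, SD 12 and r = 0.8 the chance is 0.737 × (1 − 0.563) = 32%. At r = 0.6 it is 0.967 × (1 − 0.874) = 12%. Both assume entry on the 24-hour reading. That is possible, not likely.
- A reader might add season, since "Baseline data collection was completed in January 2014. Follow-up data collection was completed in August 2014". The article does not say when follow-up began and gives neither size nor direction for a seasonal effect.

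Finally, a within-arm confidence interval is shifted by regression to the mean just as a test is. That is correct: adjusting the interval cures only the clustering, so it also needs a statement of what it does not show.

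**Conclusion.** The point holds in two parts. The paired tests do not keep their stated level if changes correlate within practices: about 9.4% and 7.8% at an assumed ICC of 0.05, and about 5.5% to 14% over 0.01 to 0.10. This rests on 12 recruiting practices per arm of equal size and complete follow-up. Independently of clustering, a significant within-arm fall is not evidence of an intervention effect, because selection and participation may lower blood pressure in either arm. The size of that shared fall cannot be fixed from the article. It could be several mmHg if most patients qualified on the baseline 24-hour reading, and near zero if they qualified on separate office readings. The sponsor should correct this, but it leaves the primary analysis as it is.

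**What to change.** Replace the within-arm significance tests with mean changes per arm and cluster-adjusted 95% confidence intervals, labelled descriptive and not to be read as intervention effects. Word the cluster-adjusted between-arm comparison on change in blood pressure, or on follow-up blood pressure adjusted for baseline, and state that it carries all inference on the change endpoint. Both edits are needed: deleting the paired tests alone would leave no test worded on change.

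The cost is a little more analysis work and no new data. At ICC 0.05 the within-arm intervals widen by about 17% and 11% (√1.37 = 1.17, √1.23 = 1.11), before any allowance for having only 12 practices per arm. It would also help to report how many patients qualified by each route and whether the qualifying 24-hour reading was used as baseline.

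### The key secondary endpoint is change in blood pressure, but the only between-arm test in mmHg compares levels, names no visit and leaves the baseline reading unused

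*Protocol article*

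**What the plan says.** The Outcome measures section of the protocol article states: "The key secondary endpoints are the changes in average systolic and/or diastolic blood pressure (in mmHg". On timing it adds: "All outcomes are measured at baseline (before the intervention) and at follow-up (3 months after the last education session) in both study arms". The paired data exist for every patient by design, since "each study patient receives a 24-hour ambulatory blood pressure monitoring at baseline and at follow-up".

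The section on statistical hypotheses, methods and analyses plans three things that bear on this endpoint:

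- **Within arms, change is tested.** "Differences between baseline and follow-up will be tested for significance within each study arm using paired t-tests".
- **Between arms, the level is tested.** The method is a t-test for two independent groups, modified to allow for clustering by practice. What it compares is given as "Differences in the mean systolic and diastolic blood pressure level of patients of the intervention group and patients of the control group". Just before this, the section says that average levels will be determined at both visits, so the word level does not by itself fix the visit.
- **A mixed model with a different outcome.** "A generalized linear mixed model will be performed to identify predictors on blood pressure control at follow-up". Its covariates are an open list that begins "patient level covariates such as age, sex, lifestyle, comorbidities". Baseline blood pressure is not named in it.

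**The concern.** The endpoint and the test do not match. The endpoint is a change, and the only comparison of change runs inside each arm. The only comparison between arms is of something else, at an unnamed visit. The mixed model does not close the gap, because its outcome is control or no control, not mmHg.

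Two things are at stake. The first is precision: a baseline reading of the same measure is available for each patient, and the between-arm test does not use it. The second is chance imbalance. Only 24 practices were randomized, enrolment was unequal (101 of 169 patients in the intervention arm, so 68 in control), and patients could qualify by office, 24-hour or home readings. The arms can therefore differ in baseline 24-hour pressure by chance, and a comparison of follow-up levels carries part of that difference into the estimated effect.

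There is also a risk in reporting. If change is tested only within arms, readers will be drawn to compare two within-arm P values, which is not a test of the intervention.

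**Working it through.** The article gives no standard deviation, correlation, power or precision figure for the mmHg endpoint, so there is no stated figure to reproduce. The check shows how the size depends on what is not given.

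**Inputs from the article:** 169 patients (101 and 68), 24 practices, so 169/24 ≈ 7 patients per practice; ICC 0.05 (sample size section, stated for the binary endpoint and so an assumption here).

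**Assumed:** baseline to follow-up correlation r of 0.3 to 0.7; equal standard deviations at the two visits; comparison at follow-up, the natural reading of the between-arm test.

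**Step 1: r equal at patient and practice level.** Relative to follow-up level alone, the variance of the between-arm contrast is 1 − r² with baseline as covariate and 2(1 − r) for an unadjusted change score. The design effect cancels.

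| r | Variance cut by adjustment (r²) | SE smaller by 1 − √(1 − r²) | Change-score variance ratio 2(1 − r) |
|---|---|---|---|
| 0.3 | 9% | 5% | 1.40 |
| 0.5 | 25% | 13% | 1.00 |
| 0.7 | 49% | 29% | 0.60 |

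An unadjusted change score, the literal match to the endpoint, gains nothing at r = 0.5 and loses precision below it.

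**Step 2: only patient-level variance falls.** The variance of a practice mean is proportional to 0.05 + 0.95/7 = 0.186.

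- r = 0.5: 0.05 + 0.75 × 0.95/7 = 0.152, which is 18% less variance; the SE is about 10% smaller.
- r = 0.7: 0.05 + 0.51 × 0.95/7 = 0.119, which is 36% less variance; the SE is about 20% smaller.

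**Step 3: selection on baseline.** Patients enter because their pressure is uncontrolled, which tends to lower r. As an illustration, keeping only patients above the mean of a normal distribution takes an unselected r of 0.5, 0.6 and 0.7 to about 0.33, 0.41 and 0.51. The variance cut in Step 1 is then about 11%, 17% and 26%.

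**Step 4: chance imbalance.** Assume a 24-hour standard deviation of 10 to 15 mmHg.

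- Design effect: 1 + (169/24 − 1) × 0.05 = 1.30.
- SE of the baseline arm difference: SD × √[(1/101 + 1/68) × 1.30] ≈ 0.179 × SD, or about 1.8 to 2.7 mmHg.
- Probability of a chance difference of at least 3 mmHg in either direction: about 9% to 26%.
- Part of a 3 mmHg imbalance left in the level comparison: r × 3 = 0.9, 1.5 and 2.1 mmHg at r = 0.3, 0.5 and 0.7.

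For scale, the Discussion cites systolic differences of −1.75 and −4.76 mmHg from the two practice-redesign trials that it treats as closest.

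**The case against.** The strongest reply is that the level test is sound. With arms alike in expectation at baseline, the difference in follow-up means and the difference in mean changes have the same expected value, and the planned test allows for clustering. This stands. A reader might infer that the test is invalid or cannot speak to the endpoint; the article does not support that. The test is inefficient and not worded for the endpoint.

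A reader might also infer that a quarter to a half of the precision is lost. That needs r of about 0.5 to 0.7, on the variance scale, with the same correlation at practice level. The article gives no correlation, selection on high pressure may lower it, and Step 2 shows smaller gains if practice-level variance does not fall. Nor is a baseline difference carried over in full: the expected carry-over is r times the difference.

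It can further be said that covariate choice for a secondary endpoint belongs in an analysis plan that is not shown. That is fair for a detail left open. Here, however, the article itself names the between-arm test, and that test does not match the endpoint that it defines.

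Finally, the precision argument favours baseline adjustment and does not follow from the wording mismatch alone. This too stands: simply switching to change scores could make matters worse.

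**Conclusion.** The point holds as a mismatch between endpoint and analysis, with avoidable inefficiency. The endpoint is change; the one between-arm mmHg test compares levels, with no visit and no baseline term; change is compared only within arms.

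The size cannot be fixed from the article. With equal correlation at both levels, adjustment would cut the variance by 9% to 49% over an assumed r of 0.3 to 0.7. If only patient-level variance falls, the SE gain is about 10% to 20% at r of 0.5 to 0.7. The imbalance figures rest in addition on the assumed standard deviation and on an ICC borrowed from the binary endpoint. None of this makes the planned comparison biased under randomization. It is worth correcting because the endpoint is a key secondary one and the data needed are collected anyway.

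**What to change.** Replace the between-arm t-test with a linear mixed model of follow-up 24-hour systolic pressure on arm and baseline 24-hour systolic pressure, with a practice random intercept and small-sample (Satterthwaite-type) degrees of freedom. Fit a separate model of the same form for diastolic pressure. Report the adjusted mean difference with its 95% confidence interval as the between-arm effect on change. With baseline in the model, the arm coefficient is the same whether the outcome is follow-up pressure or change, so this answers the endpoint as defined. State that the within-arm paired tests are descriptive only.

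The cost is a few sentences and no new data: both readings are planned for every patient and merged per patient, and random-effects modelling is already intended. The Trial status section reports follow-up as complete and data management as ongoing, so the change needs a dated record that it was made before outcome analysis.
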